### Intervention

The intervention begins immediately after the first postoperative consultation. Participants in both groups are advised to attend individual face-to-face sessions with a physiotherapist at a rehabilitation clinic and any postoperative consultation with the orthopaedist. We acknowledge that there may be accessibility issues in face-to-face sessions^7 9^ and variations in content and exposure^4^ that could impact our results. We randomly assigned both groups under comparable circumstances in our trial protocol to account for this. While we cannot control face-to-face sessions, we will monitor attendance and coverage weekly for both groups using a short messaging service. Additionally, we will strive to monitor the content similarity between face-to-face and remote sessions.

The intervention consists of internet-based synchronous remote sessions using videoconferencing software and face-to-face sessions. This enables participants to engage in therapeutic exercises at home under the guidance of an exercise and health coach. The remote sessions take place over 22 weeks, 3 days a week, lasting 40 min.

To provide a comprehensive description of the intervention, we have developed table 1 under the Template for Intervention Description and Replication recommendations.^18^

**Table 1 T1:** Intervention description

Item	Comparison arm	Intervention arm
Brief name	Clinic-based rehabilitation	KC@H programme
Where	Rehabilitation clinic	Rehabilitation clinic and patient home
How	Face-to-face sessions	Face-to-face and remote sessions
Who	Physiotherapist	Physiotherapist and exercise and health coach
What	Dependent on rehabilitation clinic protocol and physiotherapist judgement	(face-to-face sessions) Dependent on rehabilitation clinic protocol and physiotherapist judgement. (remote sessions) KC@H manual providing general information, therapeutic exercises, time-based standards and criterion-based standards for progression
When	Starting from the second week after ACLR	Starting from the second week after ACLR
How much	Expected to last for 22 weeks, the number of sessions will be dependent on the patient’s preference and the availability of the rehabilitation clinic	(face-to-face sessions) Expected to last for 22 weeks, the number of sessions will depend on the patient’s preference and the availability of the rehabilitation clinic. (remote sessions) The programme will last for 22 weeks, with three sessions per week, each lasting 40 min. The exercise load will be monitored using the CR10 scale, while the pain intensity will be assessed using the VAS at the beginning and end of each session.
Tailoring/modifications	None	Time-based standards: immediate stage (0–2 weeks); early stage (2–4 weeks); intermediate stage (4–12 weeks); late stage (12–16 weeks); final stage (16–24 weeks) Criterion-based standards: inflammatory response; range of motion; lower limb muscle strength; gait; balance; core stability; agility; plyometrics

ACLR, ACL reconstruction; CR10, Borg Category Ratio Scale; KC@H, Knee Care at Home; VAS, Visual Analogue Scale.

#### KC@H programme manual

The KC@H manual describes all therapeutic exercises included in the programme, with patient progression determined based on objective criteria rather than a predetermined recovery timeline after ACLR.^19^ This approach, which combines time- and criterion-based standards, helps prevent adverse events during remote sessions and allows the intervention to be applied in various clinical scenarios.^19^

Due to the unavailability of specialised strength equipment for our remote sessions, we have used the CR10 scale to monitor training load and progress. For every exercise, we will record the duration (in minutes), number of sets and repetitions and the level of completion (complete, incomplete, unable to perform). Additionally, we will document the pain intensity at the start and end of each remote session. The orthopaedist will receive a detailed progress report containing all the information gathered during the remote sessions.

#### Postoperative phases

The postoperative period following ACLR lasts 24 weeks and is divided into five stages. The first stage, known as the ‘immediate postoperative’ stage, begins immediately after surgery and lasts 2 weeks. Although this stage starts before our trial intervention, the KC@H manual includes self-care recommendations developed by orthopaedic surgeons from HME. The baseline evaluation (t_0_) is conducted at the end of this stage, during the first postoperative consultation.

The second stage, which coincides with the start of our trial intervention, is called the ‘early postoperative’ stage. It begins immediately after our baseline evaluation and lasts 2 weeks until the next consultation with the orthopaedist (t_1_) in the fourth week after hospital discharge. This is the only intervention period that lasts less than 4 weeks.

After the early postoperative stage, the third stage, referred to as the ‘intermediate postoperative’ stage, is then divided into two substages, each lasting 4 weeks. At the end of each substage, a consultation with the orthopaedist and subsequent evaluation occurs at the 8th (t_2_) and 12th (t_3_) weeks.

The fourth stage, ‘late postoperative’, begins immediately after t_3_ and continues for 4 weeks. At week 16, another consultation with the orthopaedist (t_4_) is scheduled. The final stage, ‘final postoperative’, is divided into two substages, each lasting 4 weeks. Following t_4_, a consultation with the orthopaedist and subsequent evaluation occurs on the 20th (t_5_) and 24th (t_6_) weeks after hospital discharge. The 24th-week consultation marks the end of the intervention.

Additionally, patients in both groups will be invited for a scheduled follow-up at the end of the postoperative period, approximately at week 36 (9 months) after hospital discharge and 12 weeks (3 months) after the conclusion of the trial intervention (f_1_).

#### Outcomes measures and assessments

Outcome measures will be assessed during scheduled consultations with the orthopaedist. The exercise and health coach will record pain intensity and physical exertion during each remote session. A physiotherapist (assessor) will remain consistent for every evaluation and conduct assessments during consultations with the orthopaedist.

The outcome measures and assessment tools for both groups are categorised into patient-reported (table 2), clinician-reported (table 3), physical functional performance and clinical relevance (table 4). These tables outline the procedures for each outcome measure and the tools used in the evaluations.

**Table 2 T2:** Patient-reported outcome measures

Outcome	Assessment tool	Procedures
Knee pain during the last 24 hours	Visual Analogue Scale^16^	Patients provide feedback on knee pain intensity by marking a point on a 100 mm straight horizontal line. The beginning of the line represents ‘no pain’, while the end represents the ‘worst possible pain’. A ruler measures the distance (millimetres) from 0 to the patient’s marking. A numerical value and Wong-Baker faces scale will also be presented to the patient for reference.
Knee pain during the last week	Knee Injury and Osteoarthritis Outcome Score (KOOS)^22^	Patients provide feedback on the severity of their knee pain using a standard 5-point Likert scale. Each response option is assigned a numerical value (0 for none, 1 for mild, 2 for moderate, 3 for severe and 4 for extreme). A score of 0 indicates no pain, while a score of 32 (based on 8 questions) indicates extreme pain.
Knee symptoms and stiffness during the last week	KOOS^22^	Patients are asked to rate their knee symptoms and stiffness using a standard 5-point Likert scale, with each response option assigned a numerical value (0, 1, 2, 3, 4). A score of 0 indicates total absence of symptoms, while a score of 20 (based on 5 questions) indicates constant symptoms. For knee stiffness, a score of 0 indicates total absence, while a score of 8 (based on 2 questions) indicates extreme stiffness.
Knee-related physical function during the last week	Knee Injury and Osteoarthritis Outcome Score—Physical Function Short Form^23^	Patients use a standard 5-point Likert scale to provide feedback on their knee-related physical function. Each response option is assigned a numerical value (0 for none, 1 for mild, 2 for moderate, 3 for severe and 4 for extreme). A score of 0 indicates no difficulties, while a 28 (based on 7 questions) indicates extreme difficulties.
Knee function (daily living, sports and recreational activities) during the last week	KOOS^22^	Patients are asked to rate their knee function in daily living, sports and recreational activities using a 5-point Likert scale. Each response option is given a numerical value (0 for none, 1 for mild, 2 for moderate, 3 for severe and 4 for extreme). For knee function in daily living, a score of 0 indicates no difficulties, while a score of 68 (based on 17 questions) indicates extreme difficulties. Similarly, for knee function in sports and recreational activities, a score of 0 indicates no difficulties, while a score of 20 (based on 5 questions) indicates extreme difficulties.
Knee-related quality of life during the last week	KOOS^22^	Patients using a standard 5-point Likert scale to provide feedback on their knee-related quality of life. Each response option is given a numerical value (0, 1, 2, 3, 4), and a raw score is determined based on their responses. A score of 0 indicates no impact, while a score of 4 (based on 4 questions) indicates extreme impact on the quality of life.
Pain catastrophising	Pain Catastrophizing Scale^24^	Patients are asked to provide feedback on their thoughts, feelings or perceptions related to pain using a standard 5-point Likert scale. Each response option is assigned a numerical value (0 for ‘not at all’, 1 for ‘a slight degree’, 2 for ‘moderate degree’, 3 for ‘great degree’ and 4 for ‘all the time’). A score of 0 indicates a total absence of catastrophic thinking, while a score of 52 (based on 13 questions) indicates a persistent tendency towards catastrophising thoughts about pain.
Anxiety, depression and stress during last week	Depression Anxiety Stress Scales (DASS-21) short-form^25^	Patients use a standard 4-point Likert scale to report their levels of depression, anxiety and stress. Each response option is assigned a numerical value (0 for ‘did not apply to me at all’, 1 for ‘applied to me to some degree or some of the time’, 2 for ‘applied to me to a considerable degree or a good part of the time’ and 3 for ‘applied to me very much or most of the time’). Cut-off scores are used to determine the severity of the patient’s condition. For depression, based on 7 items, scores of 0 to 9 are considered normal, 10 to 13 are mild, 14 to 20 are moderate, 21 to 27 are severe and 28 or higher are extremely severe. For anxiety, based on 7 items, scores of 0 to 7 are normal, 8 to 9 are mild, 10 to 14 are moderate, 15 to 19 are severe and 20 or higher are extremely severe. Based on 7 items for stress, scores of 0 to 14 are normal, 15 to 18 are mild, 19 to 25 are moderate, 26 to 33 are severe and 34 or higher are extremely severe.

**Table 3 T3:** Clinician-reported outcome measures

Outcome	Assessment tool	Procedures
Height	Stadiometer	Patients are measured for standing height in centimetres using a stadiometer placed against the wall. They are instructed to stand with their backs against the wall, heels together, head in a natural position, legs straight, arms at their sides and shoulders relaxed. They should not wear shoes or heavy clothing that could affect their height measurement. The measurement arm is lowered to rest gently on the patient’s head, and the measurement is rounded off to the nearest decimal.
Weight (body mass)	Analogue Scale	A traditional weighing scale assesses patients for weight (body mass in kilograms). The scale is placed on a flat and stable surface, and patients are advised not to wear shoes or heavy clothing that could affect their weight measurement. They are instructed to stand still in the centre of the scale, with their feet evenly positioned and their weight evenly distributed. The weight measurement is then recorded and rounded off to the nearest decimal.
Knee joint effusion	Patellar Tap/Ballottement Test^26^	Patients are evaluated for knee effusion while lying supine on an examination table. The assessor applies downward strokes from the thigh to the leg with the non-dominant hand and then grasps the upper portion of the knee just above the patella. Using two fingers of the dominant hand, they press the patella against the femur in a posterior direction. Increased patellar waving or a spongy joint sensation indicates a positive test result for knee effusion. The test is then repeated on the opposite knee for comparison.
Passive knee flexion and extension range of motion	Hand-held Goniometry (HHG)^27^	Passive knee extension and flexion range of motion are measured in patients using a long-arm goniometer. Both knees are measured for comparison with the goniometer axis placed at the lateral epicondyle of the femur. The proximal arm of the goniometer is placed alongside the lateral midline of the femur, using the greater trochanter as a reference. In contrast, the distal arm is placed alongside the lateral midline of the fibula, using the lateral malleolus and fibular head as references. For passive knee flexion, the patient lies supine on the examination table, with the lower limbs in an anatomical position. The assessor flexes the patient’s knee through the available range of motion by sliding the patient’s foot along the table towards the pelvis and then taking the passive range of motion measurement. For passive knee extension, the patient lies in a supine position on the examination table with the lower limbs in an anatomical position and a towel under the ankle with the knee extended as far as possible. The assessor provides added pressure to the knee in the direction of extension and then takes the passive range of motion measurement.
Knee extensor and flexor muscle length	HHG^27^	The length of the knee flexors and knee extensors muscles in patients is measured using specific tests and a long-arm goniometer. The measurements are taken on both knees for comparison, with the goniometer axis placed at the lateral epicondyle of the femur. For the knee flexors muscle length (Thomas test), the patient lies in a supine position with the hip of the lower extremity to be measured and extended on the examination table. The leg is supported on the table, and the knee is just past the table’s edge (test side). The patient is asked to flex the contralateral hip and grasp the knee to the chest until the lumbar spine is felt to flatten against the table, and the measurement of knee flexion is taken (test side). For the knee flexors muscle length (prone technique), the patient lies in a prone position with both hips of the lower extremity extended on the examination table. The knee to be tested moves to maximal achieved flexion, and the measurement of knee flexion is taken (test side). For the knee extensors muscle length (distal hamstring length test), the patient lies in a supine position with the hip of the lower extremity to be measured in 90 degrees of flexion on the examination table. While the assessor helps maintain the hip position, the patient executes a knee extension, and the knee flexion is measured (test side).
Extensor and flexor isometric muscle strength	Hand-held Dynamometry^28^	The microFET2 is used to measure the isometric strength of the hamstrings and quadriceps in patients. This measurement is taken on both knees to allow for comparison. The patient is seated on an examination table with their hips and knees flexed at a 90-degree angle. The assessor stabilises the patient’s leg using the leg of the examination table as support for the hand-held dynamometer. The patient is then instructed to apply maximum force against the device. First, the patient is asked to try to extend the knee, and then they are asked to flex the knee. Three repetitions are performed for both extension and flexion.

**Table 4 T4:** Physical functional performance and clinical relevance outcome measures

Outcome	Assessment tool	Procedures
Physical functional performance		

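### Table 2 gives DASS-21 severity bands that a seven-item subscale scored 0 to 3 per item cannot reach, so the scoring rule and the bands must be reconciled

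*Protocol article*

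**What the plan says.** The rule is in the protocol article, under Outcomes measures and assessments, in the DASS-21 row of Table 2. On response format it says: "Patients use a standard 4-point Likert scale to report their levels of depression, anxiety and stress". The options are coded from 0, and the highest is "3 for ‘applied to me very much or most of the time". The bands have a declared purpose: "Cut-off scores are used to determine the severity of the patient’s condition".

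The item count and the bands are stated together for each subscale:

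- Depression: "For depression, based on 7 items, scores of 0 to 9 are considered normal", and higher up "14 to 20 are moderate, 21 to 27 are severe and 28 or higher are extremely severe".
- Anxiety: "For anxiety, based on 7 items, scores of 0 to 7 are normal", and at the top "15 to 19 are severe and 20 or higher are extremely severe".
- Stress: normal is 0 to 14 and mild 15 to 18, also on seven items; then "19 to 25 are moderate, 26 to 33 are severe and 34 or higher are extremely severe".

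Neither this row nor any other part of the article states a multiplier, rescaling or conversion. Table 5 schedules anxiety, depression and stress at nine assessments, from the preoperative consultation to week 36. Seven of these fall after the allocation visit.

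**The concern.** The cell fixes three things at once: the item values, the number of items and the cut-offs. The first two determine the largest possible sum, and the third goes well beyond it. This is therefore a conflict between stated numbers, not a detail left to a fuller document.

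An analyst who follows the cell literally would produce severity tables in which some categories are empty by construction and high scores carry milder labels than the bands seem designed to give. A reader of the results could then take the absence of severe stress as a finding about these patients. There is a second risk: if one analyst rescales and another does not, reported means and differences would sit on different scales with nothing in the text to tell them apart.

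**Working it through.** **Inputs**, all from the DASS-21 row of Table 2: highest item value 3; seven items per subscale; five severity bands for each of three subscales, 15 in all.

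**Range of a plain sum.** Maximum = items × highest item value = 7 × 3 = 21. There are 22 possible sums, 0 to 21. The stated lower limits of the top band are 28 (depression), 20 (anxiety) and 34 (stress). Only the anxiety limit lies within the range.

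**Plain sums sorted into the stated bands:**

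| Subscale | Normal | Mild | Moderate | Severe | Extremely severe |
|---|---|---|---|---|---|
| Depression | 0–9 | 10–13 | 14–20 | 21 only | none |
| Anxiety | 0–7 | 8–9 | 10–14 | 15–19 | 20–21 |
| Stress | 0–14 | 15–18 | 19–21 | none | none |

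Three of 15 bands are empty. A patient who gives the worst answer to all seven stress items scores 21 and is classed as moderate.

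**Is a plain sum the natural reading?** The same product, items × highest value, reproduces the maximum stated in the other summed rows of Table 2:

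- KOOS pain 8 × 4 = 32
- symptoms 5 × 4 = 20
- stiffness 2 × 4 = 8
- physical function short form 7 × 4 = 28
- daily living 17 × 4 = 68
- sport and recreation 5 × 4 = 20
- Pain Catastrophizing Scale 13 × 4 = 52

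The one exception is KOOS quality of life, where 4 × 4 = 16 but the table gives 4. That figure also fails the arithmetic and does not point to a rescaling rule. So the table's convention is the plain sum.

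**What a conversion would change.** To reach the top stress band, a multiplier must be at least 34 / 21 = 1.62. The article does not fix its value. Taking 2 as an assumption, the range becomes 0 to 42, every band can be reached, and the raw sums fall as follows:

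| Subscale | Normal | Mild | Moderate | Severe | Extremely severe | Sums whose band changes |
|---|---|---|---|---|---|---|
| Depression | 0–4 | 5–6 | 7–10 | 11–13 | 14–21 | 17 of 22 |
| Anxiety | 0–3 | 4 | 5–7 | 8–9 | 10–21 | 16 of 22 |
| Stress | 0–7 | 8–9 | 10–12 | 13–16 | 17–21 | 14 of 22 |

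Examples under that assumption:

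- A depression sum of 11 doubles to 22 (severe) but reads as mild unconverted.
- A depression sum of 9 doubles to 18 (moderate) but reads as normal.
- A stress sum of 14 doubles to 28 (severe) but reads as normal.

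The disagreement starts at raw sums of 5, 4 and 8 for depression, anxiety and stress, so it is not confined to extreme scores.

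**Effect on the treatment comparison.** Multiplying the score and its baseline by a constant c multiplies the estimated group difference and its standard error by c. Their ratio, and so the test, is unchanged. A distribution-based MCID (a fraction of the SD) also scales by c, so it can be read only if the scale is named.

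**The case against.** The strongest reply is that the row never says in words that the DASS-21 score is a plain sum and, unlike its neighbours, gives no maximum. Cut-offs above 21 could simply mean that a conversion step was dropped from a condensed table that cites the instrument's source. Staff may already apply it. This stands in part: whether any patient is misclassified depends on what is done in practice. It does not rescue the text, which ties its bands directly to seven items scored 0 to 3 and must be corrected either way.

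Three stronger readings are tempting, and the article does not support them:

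- **That the treatment comparison is wrong.** The Statistical analysis section plans linear mixed models adjusted for baseline and describes no comparison of severity categories. A model of the subscale score gives the same test with or without a multiplier. The sample size rests on KOOS pain.
- **That distressed patients would be overlooked in their care.** No eligibility rule, referral or treatment decision in the article uses a DASS-21 band. The related exclusion criterion concerns medication for mental health disorders.
- **That doubling is the correct rule.** The article does not say so. A factor of 2 makes all bands reachable, but it has to be confirmed from the instrument's scoring source.

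**Conclusion.** The contradiction is certain and follows from the article's own numbers: a subscale range of 0 to 21 against bands that start as high as 28 for depression and 34 for stress. Followed as written, three of 15 bands are empty, severe depression and extremely severe anxiety occur only at or next to the maximum, and the worst possible stress score is called moderate. Because the rule is the same for all participants, any understatement of severity affects both arms.

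Two parts are conditional. Misclassification occurs only if the bands are applied to unconverted sums. The counts of 17, 16 and 14 changed sums rest on the assumed factor of 2, and they count possible scores, not expected patients. The consequence is limited to the severity categories and to how means, differences and any MCID on this measure are read. It is worth correcting because the rule as stated gives wrong labels and the correction is very cheap.

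**What to change.** Before analysis, reconcile the scoring rule with the bands in the DASS-21 row of Table 2, in one of two ways:

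- State the conversion applied to the seven-item sum before the listed cut-offs are used. Doubling to 0–42 is one candidate, to be checked against the instrument's scoring source.
- Keep the plain sum and give integer cut-offs that fit 0 to 21. Halving the listed limits is not enough unless rounding is specified, since 9 / 2 = 4.5, for example.

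In either case, add which scale is used for reported means, between-group differences and any MCID. The planned mixed models on the score need no change. The cost is one or two sentences in Table 2 and one line of scoring code.
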